### Development of the analytic matrix

We first mapped the Obrist dimensions to the service domains identified by Levesque *et al* (online supplemental table 1). Next, we selected domain descriptors that we felt captured the essence of each unique element from across the two frameworks (online supplemental table 2). We felt that ‘availability’ domain by Levesque *et al* straddled two different concepts: those related to distance/transport and facilities. Next, we added in the domains that pertain to users, mapping them to the service domains and providing a unified descriptor (online supplemental table 3). The framework by Levesque *et al* identified three areas that do not naturally correspond with service characteristics: themes around the desire to seek care, the capacity to participate in care (eg, though shared decision-making with a clinician or medication concordance) and empowerment and social support. Next, we mapped the common barriers that were identified in our literature review of the existing eye care literature to the unified descriptors of service and user domains (online supplemental table 4). Finally, we reconfigured this table to create a deductive template that can be used to enter quotes during and directly after each interview. The whole point of using interviews rather than a (much faster and less expensive) survey approach is to be able to uncover barriers and potential solutions that the research team had not previously considered. As such, the template, interview prompts and data collector training all emphasise the ‘other’ column. figure 4 illustrates our analytic matrix.

**Figure 4 F4:**
[figure not shown]
The analytic matrix.

### Process for completing the matrix

During the interview, data collectors will expand the column width for the relevant interviewee number (eg, interviewee 1). They will type short quotes on each barrier into the relevant row, using the participant’s own words. Data collectors will repeat the process when asking for potential interventions that would have made it possible to attend, adding ideas to the matrix. They will probe for further forms of service modification (which we are able to change) that would make a tangible difference.

Directly after the interview, the data collectors will listen back to the audio recording of the interview and expand on and correct the quotes that they noted during the interview. All quotes will be directly translated into English. Data collectors will replace the ‘subtheme n’ text in the barriers and solutions columns with add their own (inductive) codes, for instance, ‘long queue at clinic’, ‘cost of spectacles’ or ‘rumours of inexperienced staff’. The number of subthemes is not limited; new rows can be added as required. As stated above, after a minimum of 14, interviews will continue until no new subthemes emerge from two successive interviews. Data collectors will debrief with experienced national qualitative research leads each day in person or online. The national leads and the international research manager will collaboratively check quality and consistency of data entry, review all quotes and subthemes and assess when thematic saturation has been reached. Once qualitative data analysis is complete, all audio recordings will be deleted.

### Use of findings

Once saturation is reached in a given programme, the research team will use the full matrix to generate a list of all the individual barriers and solutions that arose from the interviews. These may include things like sending SMS reminders, reducing the distance that people have to travel or altering the way that people are counselled before being referred.

The long list of solutions will be reviewed by the local programme funder and programme implementer to rule out any service modifications that are completely unfeasible—such as paying people US$100 to attend, or providing free individual transport for every participant. The short list of potential service modifications will form the basis of a survey that will be sent to a wider sample of non-attenders in order to identify the most promising actions at a generalisable level. Each programme will generate its own list of barriers and solutions.

### Survey

Once we have generated a list of potential solutions, we will perform a survey to rank these in terms of perceived impact. Again, this approach is programme specific. At no point are we applying findings from one programme to another. As stated above, we will have a complete list of every non-attender belonging to the sociodemographic group with the lowest overall attendance rate. We will administer a telephone survey to a representative sample of non-attenders from this group, excluding all of those who have already been interviewed. We will use a 95% CI, a 5% margin of error and a conservative assumption that the total population size is 1 million people (with the same characteristics as the most marginalised group). This renders a sample size of 384.

We will use computer-generated numbers to obtain a random sample of non-attenders to call. Data collectors will seek verbal audio recorded consent before reading through the full list of potential service modifications that arose from the interview stage. Respondents will be asked to rank each suggestion from 1 to 3 on a simple Likert scale:

It would make a big difference, that is, if we introduced this change then you or people like you would definitely attend.It would make a moderate difference, that is, it would greatly increase the chances, but it would not be enough by itself to guarantee attendance by itself.It might make a small difference, that is, it might help a few people, but the impact is likely to be minimal.

We will calculate the average score for each service modification and generate a ranked list. Workshop participants will review the ranked list and select the most promising service modification to implement and evaluate.

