Almost all surveys use a familiar list of barriers that commonly recur in qualitative studies, including high costs, long distances, transport issues, low trust in service providers, perceptions of low service quality, communication challenges, fear, scheduling issues, low awareness of services on offer, lack of a chaperone and the perception that vision impairment is not a significant impediment to function.^14^,^1820 22^ The main limitation in using surveys with these preselected items is that other important factors may be at play in a given population, but it is impossible to ascertain what they are without using open questions.^33^ Methods to elicit these barriers do not have to be particularly sophisticated: even though Sengo *et al* appear to have used relatively basic qualitative methods, their study still uncovered novel and important barriers including overcrowding in the local hospital, self-medication and the use of spectacles bought on the street.^30^ Similarly, while the method outlined by Marmamula *et al* to interview 199 elderly non-attenders provided no reference to theory, no underlying framework and no detail on the analytical approach, the work proved vital to understanding local contextual issues, with two-thirds of respondents citing novel barriers including lack of family consent and the adverse impact of other health conditions.^34^ These factors would not have been elicited from participants through a standard survey.

When are *any data* better than *no data*? Poorly designed qualitative studies can lead researchers to the wrong and sometimes harmful conclusions, just as flying blind without any understanding of the issues faced by service users can lead managers to introduce well-meaning ‘improvements’ that carry negative unintended consequences. We would argue that using appropriate, theory-driven qualitative methods with a sensible sample and well-described methods is actually a very low threshold to clear and can add real value at low cost in settings where the alternative is not using any open questions at all.

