### Workshops

Our team already has formal agreements and pre-existing working relationships with Peek programme leads, programme funders, programme implementers, eye care policymakers and community advisory boards in each location. In each country, we will invite these stakeholders plus additional representatives from the left-behind group to a 90 min workshop to review the study findings and select one or more service modifications to implement. Workshop discussion will be led in English (the working language of the project in each country) by a facilitator from our research team. The lead researcher will present a brief overview of the barriers and potential solutions suggested by non-attenders and their proxies, and then lead a discussion to explore the groups’ perceptions of which barriers they can realistically address and which solutions offer the best balance of impact (based on survey respondent scores), cost, risk and feasibility. The aim is to identify promising service modifications that can be deployed and tested using RCTs to equitably improve access to care.

The process of decision-maker group discussion aligns with rapid methods that use group discussion with the ultimate research users as a key part of data analysis, interpretation and application. The workshop will close with the identification of the most promising service modification to test and discussion of next steps.

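### The survey scale has no option for 'no difference' or 'less likely to attend', so null and deterrent views are scored the same as a slight benefit

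*Protocol article*

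**What the plan says.** The Survey section of the protocol article states the response format in full: "Respondents will be asked to rank each suggestion from 1 to 3 on a simple Likert scale". The options are:

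- Option 1: "It would make a big difference, that is, if we introduced this change then you or people like you would definitely attend".
- Option 2: "It would make a moderate difference, that is, it would greatly increase the chances", with the qualification that it would not guarantee attendance on its own.
- Option 3: "It might make a small difference, that is, it might help a few people, but the impact is likely to be minimal".

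The scoring rule follows: "We will calculate the average score for each service modification and generate a ranked list". Under Workshops, stakeholders then discuss "which solutions offer the best balance of impact (based on survey respondent scores), cost, risk and feasibility". The Methodology section gives the survey's purpose as checking the interview findings in a larger, representative group of non-attenders. The Output section makes the modification or modifications selected in this way the primary output of the study.

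**The concern.** All three options describe some degree of benefit. A respondent who thinks a modification would do nothing, or would put them off, has no option that says so. If that respondent answers, the only place left is option 3, with the code given to someone who sees a small benefit.

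This matters because of what the survey is for. The suggestions come from a small number of interviews (a minimum of 14 and a budget of 20 per location), and the larger sample is the check on whether they hold more widely. On this scale a respondent can agree more or less strongly but cannot reject an item. A modification that helps some of the group and deters others cannot be recognised from the scores, and no later analysis can recover the distinction.

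The anchors also shift. Option 1 concerns attendance by the respondent or people like them, whereas option 3 concerns help to a few people. Someone for whom an item does nothing, but who thinks that it would help many others, has no clear answer.

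**Working it through.** **The plan's own figure.** The Survey section states: "We will use a 95% CI, a 5% margin of error and a conservative assumption that the total population size is 1 million people". With z = 1.96 and p = 0.5 (assumed; the article does not give it), n0 = z² × p(1 − p) / e² = 1.96² × 0.25 / 0.05² ≈ 384.15. With the finite population correction, n = n0 / (1 + (n0 − 1) / 1,000,000) = 384.00. The stated 384 reproduces and is not affected by this point.

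**What the mean can see.** Let b be the share choosing big (code 1) and m the share choosing moderate (code 2). Suppose that everyone else, whether their view is small benefit, no effect or deterrence, chooses option 3. Then

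mean = 1 × b + 2 × m + 3 × (1 − b − m) = 3 − 2b − m.

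How the remaining respondents divide between small benefit, no effect and deterrence drops out. With b = m = 0 the mean is 3.00, whichever of the three views everyone holds. On an extended code (4 = no difference, 5 = less likely to attend), the same three cases score 3, 4 and 5. This result needs no assumption beyond respondents using the nearest option.

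**Items with divided opinion.** The distributions below are assumed, for illustration only.

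| Item | Big | Moderate | Small | None | Less likely | Mean, stated scale | Mean, extended code |
|---|---|---|---|---|---|---|---|
| P | 30% | 20% | 50% | 0% | 0% | 2.20 | 2.20 |
| Q | 30% | 20% | 0% | 50% | 0% | 2.20 | 2.70 |
| R | 35% | 20% | 0% | 15% | 30% | 2.10 | 2.85 |

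- P, both scales: 0.30 + 0.40 + 1.50 = 2.20.
- Q, extended: 0.30 + 0.40 + 2.00 = 2.70.
- R, stated scale: 0.35 + 0.40 + 3 × 0.45 = 2.10. Extended: 0.35 + 0.40 + 4 × 0.15 + 5 × 0.30 = 2.85.

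On the stated scale P and Q tie, and R, which deters 30%, comes first because a lower score is better. On the extended code R comes last. The 0.10 gap between R and P on the stated scale is itself small: at n = 384 the 95% half-width of one item mean is 1.96 × SD / √384, or 0.06 to 0.10 for assumed SDs of 0.6 to 1.0.

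**How far a change of order can be trusted.** Take S = 30/10/10/50% and T = 15/30/55/0% (big/moderate/small/none).

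- Stated scale: S = 0.30 + 0.20 + 3 × 0.60 = 2.30; T = 0.15 + 0.60 + 3 × 0.55 = 2.40. S leads.
- Four equally spaced codes: S = 0.30 + 0.20 + 0.30 + 2.00 = 2.80; T = 2.40. T leads.
- Assumed attendance weights 1/0.5/0.1/0 (higher is better): S = 0.30 + 0.05 + 0.01 = 0.360; T = 0.15 + 0.15 + 0.055 = 0.355. S leads, narrowly.
- The same weights with moderate at 0.6: S = 0.30 + 0.06 + 0.01 = 0.370; T = 0.15 + 0.18 + 0.055 = 0.385. T leads.

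The order therefore depends on the assumed spacing as well as on the assumed distributions.

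**The case against.** The strongest reply is that option 3 is close to a null response. It is hedged and calls the likely impact minimal, so a respondent who sees no value has an obvious place to go, and an item that everyone finds useless gets the worst possible score. This stands, and it limits the damage to items with divided opinion.

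There are further safeguards. Every item was proposed by non-attenders from the same group or their proxies. The workshop also weighs cost, risk and feasibility and includes representatives of that group. The chosen modification then goes into a randomised trial. These checks are real, but none supplies survey data on deterrence.

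The questionnaire itself is not shown, so a rule for unanswered items may exist. If null views were left blank and dropped, however, item Q would score (0.30 + 0.40) / 0.50 = 1.40, which flatters it further.

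A reader might infer more than the article supports:

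- That impact is overstated. The means are used to order items, not to estimate an effect on attendance.
- That an item with every answer at option 3 or better helps everyone. Option 3 does not claim that.
- That the change of order proves the planned ranking wrong. The last calculation shows that it does not.
- That the authors concede the problem when they write that acting blindly "can lead managers to introduce well-meaning ‘improvements’ that carry negative unintended consequences". That sentence concerns acting without understanding service users, whom this study consults.
- That calling the task ranking, or giving the best item the lowest number, is an error. Both are matters of convention.

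**Conclusion.** The point holds in a limited form. The scale as written merges no effect and deterrence with slight benefit, and the averaging rule carries that merger into the workshop's impact measure. The merger is certain if respondents who hold null or negative views answer with the nearest option. Its effect on the ranking is not certain: it is confined to items on which opinion is divided, and its size cannot be derived from the article. The change of referent between options 1 and 3 adds some ambiguity to what is being rated. The sample size is unaffected. This is a worthwhile, low-cost improvement to the instrument rather than an error that invalidates the survey.

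**What to change.** Before data collection starts in Botswana, India and Nepal:

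1. Add two response options: that the change would make no difference, and that it would make attendance less likely.
2. Word all options about the same referent. This could be the respondent (or their child) or people like them, provided that it does not change between options.
3. Give the workshop the percentage in each category for every item, including the less-likely category, alongside the mean. Stakeholders can then see divided opinion without relying on a particular score spacing.

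The cost is a few seconds more per item on each call. Because the Study status section reports ethical approval for every country, revised wording may also need a minor amendment and retranslation. The approach has already been piloted in Kenya, so if survey data there were collected on the three-option scale, report them separately as such.

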## Approach

### Philosophical paradigm

Our aim requires methods that span the space between constructivist and positivist philosophical paradigms.^44^ While the task of seeking to understand perceptions of barriers and solutions is primarily phenomenological, we intend to generalise the findings (ie, make statistical inferences) and develop service modifications that will be applied across entire programmes within each country. To traverse this philosophical rift, we will use a pragmatist paradigm, originally advanced by Charles Sanders Peirce.^45 46^ Pragmatism holds that ‘truth’ is determined by practical application and consequences, and it is agnostic on the type of research techniques used as long as they answer the research question.^45 47^

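### The survey's 5% margin covers one item at a time; the ranked list of mean scores depends on differences between items, which that margin does not cover

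*Protocol article*

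**What the plan says.** The protocol article's Survey section gives the sizing inputs, "We will use a 95% CI, a 5% margin of error and a conservative assumption that the total population size is 1 million people", and the result, "This renders a sample size of 384". It does not say which quantity the 5% refers to. The survey is run and ranked separately in each programme ("Again, this approach is programme specific").

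Each respondent hears the full list of modifications and scores every one: "Respondents will be asked to rank each suggestion from 1 to 3 on a simple Likert scale". In the order printed, 1 is the strongest answer (people would definitely attend), 2 a substantial but insufficient help, and 3 a minimal effect. A lower mean is therefore better. The stated analysis is "We will calculate the average score for each service modification and generate a ranked list".

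The list is then used for a decision: "Workshop participants will review the ranked list and select the most promising service modification to implement and evaluate". Under Workshops, the group discusses "which solutions offer the best balance of impact (based on survey respondent scores), cost, risk and feasibility". The Philosophical paradigm section states the inferential aim: "we intend to generalise the findings (ie, make statistical inferences".

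**The concern.** A margin of error for one quantity says how well that quantity is known. A ranking turns on whether one item's mean differs from another's, and the sizing statement does not address that comparison. A reader who sees 95% and 5% beside a ranked list may take the order to be established to that precision.

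The summary itself raises a second issue. Averaging the codes treats the step from 1 to 2 as equal to the step from 2 to 3, although the first separates certain attendance from something short of it. Two items with nearly the same mean can have very different answer patterns.

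The scores stand for impact at the workshop, and the workshop's selection is the study's primary output (Output section). The later trial tests only what was selected, so it cannot recover a modification that was placed too low and passed over.

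**Working it through.** **Inputs from the article:** 95% confidence (z = 1.96), margin 0.05, N = 1,000,000, n = 384, scale 1 to 3. **Assumed, because the article gives none:** p = 0.5, the SD of a score, the correlation between two items scored by the same person, the number of items and their spacing.

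**1. Reproducing 384.** n0 = 1.96² × 0.5 × 0.5 / 0.05² = 384.16. With the finite population correction, 384.16 / (1 + 383.16/1,000,000) = 384.01. This matches. It requires p = 0.5 (p = 0.3 gives 323, p = 0.1 gives 138), so 384 is the worst-case size for one proportion.

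**2. What 384 gives for one mean.** The half-width is 1.96 × SD / √384, and √384 = 19.60.
- SD 0.67: 0.067 points.
- SD 1.0, the practical maximum on a 1–3 scale: 0.100 points, or 0.100/2 = 5% of the 2-point range.

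Rescaled to 0–1, the score has variance at most 0.25, the same worst case as a proportion. The 5% therefore holds for a single mean too.

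**3. What 384 gives for a difference between two items.** SD of the difference = SD × √(2(1 − ρ)).
- SD 0.7, ρ 0.3: 0.7 × √1.4 = 0.828. The half-width is 1.96 × 0.828 / 19.60 = 0.083 points.
- Over SD 0.67 to 1.0 and ρ 0 to 0.7, the half-width runs from 0.052 to 0.141.

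**4. Chance that two items come out in the wrong order** (SD 0.7, ρ 0.3; standard error 0.828/19.60 = 0.0423), from Φ(−gap/0.0423):
- true gap 0.02: Φ(−0.47) = 0.32
- true gap 0.05: Φ(−1.18) = 0.12
- true gap 0.10: Φ(−2.37) = 0.009

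For a gap of 0.10 this chance stays between about 0 and 8% over the SD and ρ range in step 3.

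**5. The top of the list.** Simulation with n = 384, latent-normal three-level answers, latent correlation 0.3 and true means evenly spaced from 1.4 to 2.0:
- 15 items (spacing 0.6/14 = 0.043): the true best item ranks first in about 84–87% of surveys.
- 20 items (spacing 0.6/19 = 0.032): about 75–77%.

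The observed top item is thus not the true one in roughly 13–25% of surveys. About two to three items, counting the top one, cannot be separated from the top. The results move by a few points with the assumed cut-points between answers.

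**6. Polarised answers (constructed example).** Item A: 45% code 1, 0% code 2, 55% code 3; mean 0.45 + 0 + 1.65 = 2.10. Item B: 0%, 95%, 5%; mean 0 + 1.90 + 0.15 = 2.05. B ranks better although nobody gave it the strongest answer. A larger sample would not change this, because it comes from the summary measure.

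**The case against.** Three stronger readings are tempting, and the article does not support them.

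- **A reader might infer that the stated precision does not apply at all, or that 384 is too small.** Step 2 shows otherwise: each mean is known to within 5% of the scale range or better, and gaps of 0.10 or more are mostly ordered correctly. The sample size is serviceable.
- **A reader might infer that no uncertainty will be computed.** The article is condensed and its analysis plan is not shown. It does not rule intervals out, and its aim of statistical inference points towards them. Silence on intervals is not the finding.
- **A reader might infer that the mean is wrong and the share giving the strongest answer must replace it.** That share leaves the same gap: for two items at 50%, the half-width of the difference is 1.96 × √(2 × 0.25 × 0.7 / 384) = 5.9 points at ρ 0.3, and 7.1 at ρ 0. In the simulation it found the true top item slightly less often than the mean (83–85% with 15 items, 74–75% with 20). It also has mirror-image failures. An item answered 40/0/60% would beat one answered 39/61/0%, although their means are 2.20 and 1.61. Nor does the top answer measure the respondent's own attendance, since it asks about the respondent or people like them.

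The consequences are also limited. The article describes the survey partly as a sense-check. The workshop includes representatives of the left-behind group, weighs cost, risk and feasibility, may select more than one modification, and its choice is then tested in a randomised trial.

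These points stand, and they lower the severity. They leave the mismatch in place: the sizing speaks to single items, while the stated output is an order.

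**Conclusion.** The concern holds in limited form, at moderate severity. The 384 delivers about 5 points for one proportion and at worst 5% of the range for one mean. It does not deliver 5% precision for the ranking. Under SD 0.7 and ρ 0.3, differences below about 0.08 points are not reliable. Under 15 to 20 evenly spaced items, the wrong item heads the list in roughly 13–25% of surveys. The SD, correlation, item count and spacing are assumptions. A few well-separated items would be ordered far more reliably, and tighter spacing would do worse. That the mean can hide polarised answers follows from the scale and needs no sampling assumption; how often it will happen is unknown.

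**What to change.** Keep the mean-score ranking and amend the Survey and Workshops text as follows:

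- State that the 5% margin applies to a single item and not to the order of items.
- Report 95% intervals for each item's paired difference from the top item, for example by bootstrapping respondents.
- Present items that cannot be separated from the top as one tier.
- Show the workshop, beside each mean, the share answering 'big difference' with its 95% CI.

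Ranking on that share alone is optional and a matter of judgement.

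The cost is a little more analysis and a less clear-cut list for the workshop. No extra respondents are needed. According to Study status, data collection had not begun in Botswana, India or Nepal when the manuscript was submitted, and Kenya had been piloted.
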